**3.2 Inclusion and Exclusion Criteria**

Inclusion criteria：Patients with a definite diagnosis of epilepsy, treated with SRVPA or TPM as monotherapy, between 2 to 75 years old, were enrolled in this study.

Exclusion criteria: epileptic syndromes; only acute symptomatic or non-epileptic seizures; a history of psychiatric or mood disorders; clinically significant laboratory abnormalities, including abnormal liver function, abnormal haematological system function, abnormal kidney function, abnormal endocrine system function, or heart disease; and clinician or the patient feeling that the treatment was contraindicated.

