**3. METHODOLOGY**

**3.1 Study Design**

Observational cohort design is to assess the effectiveness of SRVPA and TPM in Chinese epileptic patients.

For the patients with a definite diagnosis of epilepsy, an appropriate AED was chosen by the clinicians, taking into consideration the efficacy and adverse events of the available AEDs, the clinical characteristics and the economic status of the patient. The patients also had the right to refuse the clinicians’ prescriptions and could discuss the drugs with the clinicians to decide which AED would be chosen.

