**3.6.4 Subgroup analysis**

Age was divided into three subgroups (2-16, >16 to 49, and >49 to 75). Seizure duration was defined as the difference between the age at the first seizure and the age at enrolment in this study and was divided into five subgroups (≤1 month, >1 month to 12 months, >12 months to 5 years, >5 years to 10 years, and ＞10 years). The number of previous AEDs was divided into four subgroups (no AEDs, one AED, two AEDs, and ≥ three AEDs). Seizures at baseline denoted the number of seizures one month before the patients’ participation in this study and were divided into four subgroups (no seizures, one seizure, two to three seizures, and ≥four seizures). Cox proportional hazard models that incorporated tests for interactions were used for all prespecified subgroup analyses.

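### Earlier use or failure of the other study drug is neither restricted at entry nor separated in the Cox model, which adjusts only for how many AEDs came before

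*Protocol*

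**What the plan says.** **Choice of drug (Protocol 3.1).** The clinician selects the AED, "taking into consideration the efficacy and adverse events of the available AEDs, the clinical characteristics and the economic status of the patient". The patient shares in the decision: "The patients also had the right to refuse the clinicians’ prescriptions".

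**Entry (3.2).** Patients qualify if "treated with SRVPA or TPM as monotherapy". The exclusions include "a history of psychiatric or mood disorders; clinically significant laboratory abnormalities, including abnormal liver function", other organ-function abnormalities and heart disease, and finally "clinician or the patient feeling that the treatment was contraindicated". Earlier use of valproate or topiramate is not mentioned.

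**Earlier treatment (3.5, 3.6.3, 3.6.4).** Previous antiepileptic treatment is recorded at the first visit. For analysis it becomes a count: "The number of previous AEDs was divided into four subgroups (no AEDs, one AED, two AEDs, and ≥ three AEDs"). The final Cox model adjusts for sex, age, type of epilepsy, seizure duration, number of previous AEDs and seizures at baseline.

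**The concern.** In a cohort where the drug is chosen and not allocated, the drugs a patient has already tried are likely to influence the next choice. Someone who did badly on valproate is a natural candidate for topiramate, and the reverse. Such a patient brings two things to the comparison: a history of failure, which may predict further failure, and a group membership that partly follows from that history.

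A count of previous AEDs records that there was a history but not which drug it concerned. Two topiramate patients with one previous AED each, one who failed valproate and one who failed some third drug, get the same covariate value. If earlier failure of the comparator carries a different risk of failure, the difference stays in the estimated drug effect. The point matters more because section 1 frames the study around the first-line choice of AED, a question to which patients who already failed the comparator contribute least.

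**Working it through.** The protocol gives no figure for this point, so there is nothing to reproduce. The check has two parts.

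**1. What the text permits**

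| Question | Where | Answer |
|---|---|---|
| May a previously treated patient enter? | 3.2, 3.6.4 | Yes, up to three or more previous AEDs |
| Is earlier use or failure of the other study drug a bar? | 3.2 | No criterion |
| Is the identity of earlier drugs in the model? | 3.6.3 | No, only their number |
| Are the data collected? | 3.5 | Previous treatment is recorded at the first visit |
| Is any planned analysis free of the problem? | 3.6.4 | Yes, the stratum with no previous AEDs, but only as a subgroup |

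**2. How large the effect could be**

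Input from the protocol: 25% one-year failure on SRVPA (3.6.1), taken as the common baseline so that there is no true drug effect. Everything else is assumed: a share q of one group has k times the failure hazard, groups are equal in size, hazards are exponential, censoring is at 2 or 5 years, and no covariate is adjusted for.

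- Baseline hazard: λ = −ln(0.75) = 0.288 per year.
- Survival in a group with share q: S(t) = (1−q)·exp(−λt) + q·exp(−kλt).
- Its hazard relative to baseline: [(1−q)·exp(−λt) + k·q·exp(−kλt)] / S(t).

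For q = 0.2 and k = 2:

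- At time zero: 0.8 + 2 × 0.2 = 1.20.
- At 2 years: exp(−2λ) = 0.5625 and exp(−4λ) = 0.3164, so (0.450 + 2 × 0.0633) / (0.450 + 0.0633) = 1.12.

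The ratio falls because high-risk patients fail early and leave the risk set. The Cox HR averages over follow-up. Its large-sample value exp(β) solves ∫[f₁ − (f₁ + f₀)·p(t)]dt = 0, where f₁ and f₀ are the failure densities in the two groups and p(t) = S₁·exp(β) / (S₁·exp(β) + S₀).

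| Share in one group | Share in the other | Multiple k | HR, 2 years | HR, 5 years |
|---|---|---|---|---|
| 20% | 0% | 2 | 1.16 | 1.13 |
| 30% | 0% | 2 | 1.25 | 1.21 |
| 30% | 0% | 3 | 1.42 | 1.30 |
| 20% | 20% | 2 | 1.00 | 1.00 |

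If the other group holds 10% of such patients, the first three rows become 1.08, 1.16 and 1.26 at 2 years. A mild case, 10% in one group only with k = 1.5, cannot exceed its time-zero value of 1 + 0.1 × 0.5 = 1.05. If the excess sits in the comparator group, the HR is the reciprocal: 1/1.16 = 0.86 to 1/1.42 = 0.70 at 2 years.

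The HR named in 3.6.1 is 1.35. Only the most extreme row exceeds it, and only at 2 years. The 5-year column matters because 19 visits, half-yearly after month six, imply follow-up of several years.

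**The case against.** **Existing safeguards.** Psychiatric or mood history, abnormal organ function and heart disease exclude a patient whichever drug is chosen, so several reasons for avoiding one drug are removed from both groups. The count of previous AEDs absorbs part of any earlier-failure effect, and sex, age and type of epilepsy bear on drug choice. Patients with no previous AEDs are by definition naive to both drugs and form a prespecified subgroup. All of this stands, and it means that the figures above overstate the bias left after adjustment. It does not reach the full-cohort primary HR, where the identity of the earlier drug is still missing. The no-AED subgroup also leaves out patients who used only other AEDs, who are equally naive to the two study drugs.

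**Routine-practice cohort.** Section 3.4 ties medication to ordinary practice, and nowhere does the protocol say that it targets patients suitable for both drugs. Excluding everyone unsuitable for, or previously exposed to, either drug would narrow the cohort. That is a legitimate trade-off, so no such exclusion is asked for here.

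**Stronger readings that the text does not support.** A reader might infer that contraindication is judged only for the drug already chosen, so that patients with a single option are knowingly enrolled. The inclusion wording leans that way, but the treatment is not defined, the schedule in 3.3 ticks eligibility screening before the first prescribing visit, and 4.1 names the medicinal product as SRVPA or TPM. The term is ambiguous and no more. A reader might also infer that a patient who fails one drug in the study can re-enter under the other. Nothing provides for this, and 7.3 assigns each subject a unique code; the protocol merely does not rule it out in words.

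**Conclusion.** The point holds as a limited, cheaply repaired weakness in the primary analysis. The protocol lets patients who already used or failed one study drug enter under the other, and its adjustment set cannot tell failure of the comparator from failure of any other AED. The confounding is reduced by the safeguards that are there, but not removed.

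Neither size nor direction follows from the documents. The illustrative range of 1.16 to 1.42 at 2 years (1.13 to 1.30 at 5 years) rests on assumed shares of 20-30% in one group only, assumed hazard multiples of 2-3 and no adjustment. It shrinks when both groups hold such patients and vanishes when the shares are equal. The text shows that such patients may enter, not how many do. It therefore does not support a claim that the drug contrast is demonstrably biased.

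**What to change.** 1. **3.5 and 3.6.3:** from the previous-treatment data already taken at the first visit, code earlier use of valproate and earlier use of topiramate as two separate variables.
2. **3.6.3:** report the primary adjusted HR in patients naive to both study drugs beside the full-cohort HR. Restriction is safer than simply adding the two variables to the model: if nearly all patients with earlier valproate are in the topiramate group, and the reverse, there is little overlap from which to estimate their effect separately from that of the drug.
3. **3.2:** state that each patient is enrolled once, and say whether the treatment in the contraindication criterion means the chosen drug or either drug.

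Cost: a few sentences and two derived variables, with no new data collection and no patient excluded on account of earlier treatment. The downside is that the naive-only HR uses fewer patients and is less precise, so it should stand beside the full-cohort result, not replace it.

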**3.3 Schedule of Study Assessments for Subjects**

| Study period | | Screen | Visit1 | Visit2 | Visit3 | Visit4 | Visit5 | Visit6 | Visit7 |
| --- | --- | --- | --- | --- | --- | --- | --- | --- | --- |
| Screen by inclusion/exclusion standard | | √ |  |  |  |  |  |  |  |
| Informed consent | | √ |  |  |  |  |  |  |  |
| Demographic information | | √ |  |  |  |  |  |  |  |
| Interrogation and physical examination | | √ | √ | √ | √ | √ | √ | √ | √ |
| Prescribing | |  | √ | √ | √ | √ | √ | √ | √ |
| EEG | | √ |  |  |  |  |  |  |  |
| Safety evaluation | Blood routine examination | IN* | IN | IN | IN | IN | IN | IN | IN |
| Urine routine examination | IN | IN | IN | IN | IN | IN | IN | IN |
| Liver function test | IN | IN | IN | IN | IN | IN | IN | IN |
| Kidney function test | IN | IN | IN | IN | IN | IN | IN | IN |
| ECG | IN | IN | IN | IN | IN | IN | IN | IN |
| Fasting blood sugar test | IN | IN | IN | IN | IN | IN | IN | IN |
| CT or MRI examination | IN | IN | IN | IN | IN | IN | IN | IN |
| Record adverse events described by patients |  | √ | √ | √ | √ | √ | √ | √ |
| Drop-out reason analysis | |  | √ | √ | √ | √ | √ | √ | √ |
| Drug combination judgment | | √ | √ | √ | √ | √ | √ | √ | √ |
| Evaluation | Efficacy |  |  | √ | √ | √ | √ | √ | √ |
| Compliance |  | √ | √ | √ | √ | √ | √ | √ |
| Safety |  | √ | √ | √ | √ | √ | √ | √ |

| Study period | | Visit8 | Visit9 | Visit10 | Visit11 | Visit12 | Visit13 |
| --- | --- | --- | --- | --- | --- | --- | --- |
| Screen by inclusion/exclusion standard | |  |  |  |  |  |  |
| Informed consent | |  |  |  |  |  |  |
| Demographic information | |  |  |  |  |  |  |
| Interrogation and physical examination | | √ | √ | √ | √ | √ | √ |
| Prescribing | | √ | √ | √ | √ | √ | √ |
| EEG | |  |  |  |  |  |  |
| Study period | | √ | √ | √ | √ | √ | √ |
| Safety evaluation | Blood routine examination | IN | IN | IN | IN | IN | IN |
| Urine routine examination | IN | IN | IN | IN | IN | IN |
| Liver function test | IN | IN | IN | IN | IN | IN |
| Kidney function test | IN | IN | IN | IN | IN | IN |
| ECG | IN | IN | IN | IN | IN | IN |
| Fasting blood sugar test | IN | IN | IN | IN | IN | IN |
| CT or MRI examination | IN | IN | IN | IN | IN | IN |
| Record adverse events described by patients | √ | √ | √ | √ | √ | √ |
| Drop-out reason analysis | |  | √ | √ | √ | √ | √ |
| Drug combination judgment | |  | √ | √ | √ | √ | √ |
| Evaluation | Efficacy | √ | √ | √ | √ | √ | √ |
| Compliance | √ | √ | √ | √ | √ | √ |
| Safety | √ | √ | √ | √ | √ | √ |

| Study period | | Visit14 | Visit15 | Visit16 | Visit17 | Visit18 | Visit19 |
| --- | --- | --- | --- | --- | --- | --- | --- |
| Screen by inclusion/exclusion standard | |  |  |  |  |  |  |
| Informed consent | |  |  |  |  |  |  |
| Demographic information | |  |  |  |  |  |  |
| Interrogation and physical examination | | √ | √ | √ | √ | √ | √ |
| Prescribing | | √ | √ | √ | √ | √ | √ |
| EEG | |  |  |  |  |  |  |
| Study period | | √ | √ | √ | √ | √ | √ |
| Safety evaluation | Blood routine examination | IN | IN | IN | IN | IN | IN |
| Urine routine examination | IN | IN | IN | IN | IN | IN |
| Liver function test | IN | IN | IN | IN | IN | IN |
| Kidney function test | IN | IN | IN | IN | IN | IN |
| ECG | IN | IN | IN | IN | IN | IN |
| Fasting blood sugar test | IN | IN | IN | IN | IN | IN |
| CT or MRI examination | IN | IN | IN | IN | IN | IN |
| Record adverse events described by patients | √ | √ | √ | √ | √ | √ |
| Drop-out reason analysis | |  | √ | √ | √ | √ | √ |
| Drug combination judgment | |  | √ | √ | √ | √ | √ |
| Evaluation | Efficacy | √ | √ | √ | √ | √ | √ |
| Compliance | √ | √ | √ | √ | √ | √ |
| Safety | √ | √ | √ | √ | √ | √ |

* IN = if necessary, which means: laboratory examinations were carried out. Electrocardiogram (ECG) examinations were also performed, if necessary.

If clinical attention was necessary, more visits were scheduled between the regularly scheduled appointments.

**3.4 Medication**

For this observational study, the medication program is totally in accord with the program which clinicians make in their routine practice. The guidelines for the initial drug dose and titration were provided as follows. In children and adolescents (ages 2-16), the initial dosage of SRVPA was 10-15 mg/kg/day, with weekly increments of 5-10 mg/kg/day, and the target dosage was 20-30 mg/kg/day; the initial dosage of topiramate was 0.5-1 mg/kg/day, with weekly increments of 0.5-1 mg/kg/day, and the target dosage was 5-9 mg/kg/day. In adults, the starting dosage of topiramate was 25 mg per night, with a weekly increment of 25 mg/day, and the target dosage was 100-250 mg/day; the initial dosage of SRVPA was 500 mg/day, with a weekly increment of 250 mg/day, and the target dosage was 1000-2000 mg/day. In general, medications were given with small initial doses, and the doses were slowly increased until the seizures were under control. Efficacy and adverse events were balanced in the adjustment of the AED dosages.

**3.5 Procedures**

The information recorded during the first visit included patient demographics, information about previous antiepileptic treatment, history of febrile seizures, birth traumas, epilepsy in first-degree family members, and neurological diseases (e.g., stroke, head injury, cortical development disorder, or intracerebral infection). A general physical examination and a neurological examination were performed. Laboratory examinations were carried out. Electrocardiogram (ECG) examinations were also performed, if necessary. Surface electroencephalography was performed on each patient to detect significant changes that might contribute to diagnosis. Computed tomography, magnetic resonance imaging and additional examinations, such as thyroid hormones, autoantibodies, and rheoencephalography, were carried out if clinically needed. Clinicians were asked to classify the types of epilepsy, epileptic syndromes, and types of seizures according to the criteria of the ILAE

The patients were asked to return for subsequent reviews at the second week, the first month, the third month, the sixth month and at successive half-year intervals from the date of initial medication. If clinical attention was necessary, more visits were scheduled between the regularly scheduled appointments. To control recall bias, each patient treated at our centres was asked to keep a medical diary with information on seizure onset, combinations with other drugs, adverse events, and hospital admissions. To control the loss of follow-up bias in the case of patients who did not appear for regular visits, follow-up data were obtained through telephone interviews or with structured questionnaire letters by mail. A patient who was lost of contact for more than one year was defined as a follow-up loss.

**3.6 Statistical Analysis**

**3.6.1 Sample Size Calculation**

Sample size calculations were based on the primary outcome. It was assumed that the treatment failure for SRVPA and topiramate were 25% and 35% after one year, respectively. In this study, SRVPA was considered as an active comparator, there needed 415 patients for each group to achieve 90% power (β=0.1) at a 0.05 significance level to detect an equivalence hazard ratio of 1.35, assuming a dropout rate of 20% for both groups during the whole study.

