**3.6.3 Statistical Analysis Methods**

Kaplan-Meier estimates were used to describe the distribution of time to treatment failure, time to first seizure, time to 12-month remission, and time to 24-month remission. The log-rank tests were used to compare survival curves. The causes for censoring in Kaplan-Meier analysis were defined as follows: patients who were lost to follow-up, patients who died but whose death had no association with AED treatment and patients who were still receiving AED treatment at the end of this study. The censoring population was regarded as having no clinical outcome observed. Cox proportional hazard models (95% confidence interval) were used to analyse the relative risks expressed as hazard ratios (HR). In the final model, potential confounders (sex, age, type of epilepsy, seizure duration, number of previous AEDs and seizures at baseline) would be adjusted. Tolerability was assessed in the ITT population. To compare the reasons leading to treatment failure between SRVPA and topiramate, Chi-square tests and Fisher’s exact tests were used. The baseline characteristics of the two groups were compared using nonparametric tests, except the data represented as mean ± standard deviation (SD), which were analysed by using student’s t-test. All of the statistical analyses were performed with SPSS v. 13.0 software for Windows, using two-sided tests with a significance level of 0.05. No interim analysis is planned for this study.

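### Section 3.6.1 is inconsistent: 25% versus 35% one-year failure is a hazard ratio of 1.50, not 1.35, and 415 per group does not follow from the stated inputs

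*Protocol*

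**What the plan says.** Section 3.6.1 sizes the study on the primary outcome, time to treatment failure (section 2.1). Its starting assumption reads: "It was assumed that the treatment failure for SRVPA and topiramate were 25% and 35% after one year, respectively". It names SRVPA as the active comparator and states that "there needed 415 patients for each group to achieve 90% power (β=0.1) at a 0.05 significance level". The target is given as "to detect an equivalence hazard ratio of 1.35, assuming a dropout rate of 20% for both groups during the whole study".

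Section 3.6.1 gives no formula, expected number of events or length of follow-up. It does not say whether its 0.05 is one- or two-sided, or whether 1.35 is an effect to be detected or a margin.

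Section 3.6.3 names log-rank tests and Cox models as the analyses, "using two-sided tests with a significance level of 0.05". Patients still on treatment are censored at the end of the study, and patients lost to follow-up are censored. Section 3.5 schedules reviews at half-year intervals after month six.

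**The concern.** The one-year failure proportions and the hazard ratio describe the same treatment contrast, so one should follow from the other. They do not agree. The number of patients should then follow from the effect, power, significance level and dropout, and it does not.

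The 90% power claim governs how a non-significant primary result is read. A reader of section 3.6.1 cannot tell whether the study was sized for a ratio of 1.35 or 1.50, and the required events differ by a factor of 467/258 = 1.8. The word equivalence adds a third possibility, under which the hypothesis itself would be different.

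**Working it through.** **Inputs.** From section 3.6.1: one-year failure 25% (SRVPA) and 35% (topiramate); HR 1.35; 415 per group; power 90%; alpha 0.05; dropout 20%, so 415 × 0.8 = 332 per group (664 in all). From section 3.6.3: two-sided tests, log-rank and Cox.

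**1. Implied hazard ratio.** Under proportional hazards, HR = ln(1 − 0.35)/ln(1 − 0.25) = ln(0.65)/ln(0.75) = 1.497. Conversely, HR 1.35 with 25% on SRVPA gives topiramate failure of 1 − 0.75^1.35 = 32.2%. Other effect measures do not give 1.35 either: the risk ratio is 0.35/0.25 = 1.40 and the odds ratio is (0.35/0.65)/(0.25/0.75) = 1.62.

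**2. Attempt to reproduce 415 per group.** Schoenfeld's formula for 1:1 groups is events = 4(1.960 + 1.2816)²/(ln HR)² = 4 × 10.507/(ln HR)². Evaluable patients per group = events/(p₁ + p₂), then divided by 0.8 for dropout.

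| Target | ln HR | Events | p₁ + p₂ at one year | Evaluable per group | After 20% dropout |
|---|---|---|---|---|---|
| HR 1.497 (25% vs 35%) | 0.4037 | 258 | 0.600 | 430 | about 537 |
| HR 1.35 (25% vs 32.2%) | 0.3001 | 467 | 0.572 | 816 | about 1,020 |

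For 25% versus 35%, Freedman's formula gives 552 per group after dropout, and a comparison of two proportions about 549. None of these is 415. Two variants come close, but each changes an input:
- 80% power instead of 90%, two proportions, two-sided: 329/0.8 = 412.
- One-sided 0.05, HR 1.497, dropout applied as a multiplier: 211 events/0.60 = 352, and 352 × 1.2 = 422.

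**3. Power at 415 per group, counting one-year events only.** Power = Φ(√(events/4) × ln HR − 1.960), for a two-sided superiority comparison.

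| Target | Dropouts contribute nothing (332 per group) | No dropout (415 per group) |
|---|---|---|
| HR 1.497 | 332 × 0.600 = 199 events; Φ(2.849 − 1.960) = 81% | 249 events; Φ(3.186 − 1.960) = 89% |
| HR 1.35 | 332 × 0.572 = 190 events; Φ(2.068 − 1.960) = 54% | 237 events; Φ(2.312 − 1.960) = 64% |

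**4. Longer follow-up.** Assume constant hazards and 332 evaluable per group with no further loss; neither assumption is in the protocol. Events by year T are 332 × [(1 − 0.75^T) + (1 − 0.75^(HR × T))].
- HR 1.497: 258 events are reached at about T = 1.4 years. At two years there are 337 events and power is 96%.
- HR 1.35: 467 events are reached at about T = 3.6 years. At two years there are 325 events and power is 77%; at four years, 489 events and 91%.

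**5. Reading 1.35 as an equivalence margin.** The assumed true ratio of 1.497 is larger than 1.35. With 199 events and a one-sided 0.05 test against the margin, power = Φ(√(199.2/4) × (0.3001 − 0.4037) − 1.645) = Φ(−2.38), about 1%. More follow-up cannot help when the assumed truth lies outside the margin.

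**The case against.** A reader might infer that the study has only 81% or 54% power, or that it is too small. The protocol does not support that. Section 3.6.1 uses one year to express a failure rate and does not set one year as the analysis horizon. Section 3.6.3 censors patients still on treatment at the end of the study. Time to 24-month remission is a secondary outcome (section 2.2), and the half-yearly schedule runs to Visit 19 (section 3.3). Under constant hazards, longer follow-up could bring power above 90% for either ratio.

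The lower power figures also treat dropout harshly. The protocol spreads the loss over the whole study ("assuming a dropout rate of 20% for both groups during the whole study"), and lost patients stay in the ITT set and are censored, so they contribute time and events. If the full 20% were lost at a constant rate within year one, 415 per group would give about 225 events and 86% power for HR 1.50. If the loss were slower, one-year power would approach 89%. For HR 1.50 the one-year shortfall may therefore be small.

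It is also fair to object that treating 1.35 as a superiority effect passes over the word equivalence. That stands as a caution about the fix, but it does not rescue the calculation (step 5).

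None of this removes the inconsistency. Follow-up and dropout have no bearing on the conflict between 1.35 and 25% versus 35%, and section 3.6.1 states no follow-up or event count from which 90% could be derived. Nor is this detail that could be left to an analysis plan: the figures that are stated conflict.

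**Conclusion.** Wrong as written. That 25% versus 35% implies 1.50 rather than 1.35 is certain under proportional hazards, which the Cox model in section 3.6.3 assumes. It does not depend on dropout, follow-up or sidedness.

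That 415 per group does not follow from 90% power, two-sided 0.05 and 20% dropout holds on the one-year failure rates. On those rates the requirement is about 537 per group for HR 1.50 or 1,020 for HR 1.35.

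The power ranges of 81% to 89% (HR 1.50) and 54% to 64% (HR 1.35) rest on a two-sided superiority test and one-year events only. They show that the stated inputs do not yield 90%; they do not measure the power of the study as run. The follow-up times of 1.4 and 3.6 years rest on assumed constant hazards and 664 evaluable patients.

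**What to change.** Keep 415 per group and restate section 3.6.1 with one consistent target:

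1. Say whether 1.35 is an effect to detect or an equivalence margin, and make the failure rates match it.
2. For a superiority comparison that matches the two-sided log-rank and Cox tests in section 3.6.3, state either HR 1.50 (25% vs 35%), with 258 events for 90% power, or HR 1.35 (25% vs about 32%), with 467 events.
3. State the follow-up and expected events, and replace the 90% with the power that 415 per group with 20% loss gives at that follow-up.
4. If equivalence is intended, restate the assumed true hazard ratio inside the margin and align the test in section 3.6.3.

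The cost is wording only, with no extra patients. The stated power may become less favourable.

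### Section 3.6.1 claims 90% power for an equivalence hazard ratio of 1.35, but its planning rates imply HR 1.50 and section 3.6.3 tests only for a difference

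*Protocol*

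**What the plan says.** Protocol section 3.6.1 contains three statements that bear on the design:

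- The planning rates: "It was assumed that the treatment failure for SRVPA and topiramate were 25% and 35% after one year, respectively".
- The role of the reference drug: "SRVPA was considered as an active comparator".
- The size and its target: "there needed 415 patients for each group to achieve 90% power (β=0.1"), followed by "at a 0.05 significance level to detect an equivalence hazard ratio of 1.35". A 20% dropout is assumed in both groups.

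It does not say whether 1.35 is a margin or an effect to be detected. It gives no lower bound, no number of events and no follow-up length.

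Section 3.6.3 gives the analysis: "The log-rank tests were used to compare survival curves". Cox models supply hazard ratios with 95% confidence intervals, and everything is done "using two-sided tests with a significance level of 0.05". The value 1.35 does not appear there. Section 1 describes a comparative aim, to support or question the move from the older drug to the newer one, and mentions no equivalence objective.

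**The concern.** An equivalence study takes as its null hypothesis that the drugs differ by at least a margin. It rejects that null when a confidence interval lies wholly inside the margin. A difference study takes HR = 1 as its null. Section 3.6.1 uses the vocabulary of the first, planning rates that fit only the second, and an effect size that does not match those rates. Section 3.6.3 then carries out the second.

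What is at stake is the meaning of the 90% power and of a null result. The aim in section 1 makes a null result informative, because finding no difference would bear on whether the newer drug should replace the older one. With the word equivalence in the sizing paragraph and a test of HR = 1 in the analysis, the protocol leaves open what p > 0.05 would mean. It also leaves p < 0.05 silent on the 1.35 figure.

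**Working it through.** **Inputs.** From section 3.6.1: one-year failure 25% and 35%; HR 1.35; 415 per group (830 in all); 90% power; alpha 0.05; dropout 20%, so 415 × 0.8 = 332 per group (664). From section 3.6.3: two-sided tests. Assumed, because not stated: proportional hazards, 1:1 allocation, SE(ln HR) = 2/√D for D events, and the values of D below.

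**1. Hazard ratio implied by the planning rates.** ln 0.65 / ln 0.75 = 1.497. On the log scale ln 1.497 = 0.404, while ln 1.35 = 0.300.

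**2. Can the 415 be reproduced?** Events for a two-sided 0.05 test with 90% power are 4(1.960 + 1.282)²/(ln HR)².

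| Basis | Events | Per group, 30% event fraction | After 20% dropout |
|---|---|---|---|
| HR 1.35 | 467 | 779 | 973 |
| HR 1.497 | 258 | 430 | 538 |
| Proportions 25% v 35% | – | 440 | 550 |

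None gives 415. The near matches each change a stated input: 80% power gives 403 to 413 after dropout, and a one-sided test at HR 1.497 gives 422 with dropout added as N × 1.2. With 415 per group, HR 1.35 needs 467/830 = 56% or 467/664 = 70% of patients to fail. At a constant 25% a year on SRVPA and HR 1.35, that takes about 2.5 or 3.6 years of follow-up per patient.

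**3. Event counts considered.** One year only: 664 × 0.30 = 199 and 830 × 0.30 = 249. Longer follow-up: 467, the number that HR 1.35 requires.

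**4. Chance of showing equivalence.** With bounds 1/1.35 = 0.74 and 1.35, and a 90% interval (z = 1.645), it is Φ((0.300 − ln HR)/SE − z) − Φ((−0.300 − ln HR)/SE + z).

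| Events | SE | True HR 1.497 | True HR 1.00 |
|---|---|---|---|
| 199 | 0.142 | 0.8% | 36% |
| 249 | 0.127 | 0.7% | 53% |
| 467 | 0.093 | 0.3% | 89% |

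At HR 1.497 the figure is 0.9% with 190 events and 0.3% with 490, so it stays below 1% throughout. A 95% interval makes it smaller still. At HR 1.00, 90% power needs 481 events with a 90% interval or 578 with a 95% interval.

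**5. Chance that the two-sided log-rank is non-significant.**

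| Events | True HR 1.35 | True HR 1.497 |
|---|---|---|
| 199 | 44% | 19% |
| 249 | 34% | 11% |
| 467 | 10% | 1% |

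The complements are the power of the planned test. On one-year counts, 415 per group gives 81% (199 events) to 89% (249 events) at HR 1.497, and 56% to 66% at HR 1.35.

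**The case against.** Four points can be made on the other side.

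- **Equivalence may only be a wrong word for a detectable difference.** Unequal planning rates, two-sided tests and the absence of a lower bound all point that way. If so, the equivalence-power figures describe a design nobody intended. This stands as a likely explanation, but it does not rescue the paragraph: 1.35 still disagrees with 25% and 35%, and the word is still wrong.
- **A reader might infer that the study cannot conclude equivalence at all.** The documents do not support that. The planned Cox HR with its 95% interval is the quantity that would be compared with a margin. What is absent is a rule for doing so, and such a rule could sit in a separate analysis plan that is not at hand. Its absence alone is no finding; the conflict between sections 3.6.1 and 3.6.3 is.
- **A reader might infer that a null result will be presented as equivalence.** No section says so. The wording leaves room for that reading, and no more can be claimed.
- **The one-year event counts are pessimistic.** This stands. Section 2.2 has a 24-month remission outcome. Section 3.3 lists visits up to Visit 19; with Visit 1 as baseline (section 4) and the schedule in section 3.5, Visit 5 is at 6 months and Visit 19 at 6 + 14 × 6 = 90 months, or 7.5 years. Events beyond one year are therefore expected. The 36% equivalence power at HR 1.00 and the 44% non-significance at HR 1.35 are low-end cases, which become 89% and 10% at 467 events. The result at HR 1.497 does not depend on this choice.

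**Conclusion.** The point holds as a contradiction in the stated basis for power. Objective (equivalence at 1.35), planning assumption (HR 1.50) and test (two-sided, HR = 1) belong to different designs, and both conflicting sections are in the protocol itself.

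The firm figure is that, under the protocol's own rates and proportional hazards, the chance of showing equivalence within 1/1.35 to 1.35 is below 1% for any count from about 190 to 490 events. The risk that a true HR of 1.35 goes undetected is anywhere from 10% to 44%, depending on an event count that the protocol does not fix.

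The estimator and its interval remain valid under either reading. What needs correcting is the hypothesis, the effect size and the claimed power.

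**What to change.** In section 3.6.1:

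1. Replace the equivalence phrase with a difference hypothesis that matches section 3.6.3: H0: HR = 1, two-sided 0.05.
2. Use one effect size. Either take HR about 1.50, consistent with 25% and 35%, with 258 events for 90% power; or keep 1.35 and state the 467 events and the follow-up needed to reach them.
3. Restate the power that 415 per group gives on that basis, with the event count, follow-up and dropout handling shown.
4. Add that a non-significant result will not be reported as equivalence.

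Report the Cox HR with its 95% interval as already planned. Do not adopt 0.74 to 1.35 as an equivalence margin unless that range is justified in its own right. Describing SRVPA as an active comparator can stay, since it fits a difference design. If equivalence really is the aim, the margin needs a justification, the decision rule must be written down, and the sample size must be recomputed with a stated follow-up.

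The cost is a few sentences and one recalculation. The downside is that a null result can no longer be presented as equivalence, and the stated power may become less favourable than 90%.
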